## Abstract

**Introduction:**

Lung cancer is the most common cancer in China, with the highest mortality rate. Surgery is the primary treatment for early lung cancer. However, patients with lung cancer have a heavy burden of symptoms within 3 months after surgery, which seriously affects their quality of life (QOL). The symptom management model based on the patient-reported outcome (PRO) is considered the best caregiving model. The clinical evidence about the symptom management of lung cancer within 3 months after the operation is very limited. Herein, we propose a randomized controlled trial to evaluate the PRO score-based monitoring and alert system for follow-up on psychological and physiological symptoms of lung cancer patients within 3 months after surgery and further investigate the effect of intervention measures based on this PRO score-based system.

**Methods and analysis:**

This multicenter, open-label, randomized, parallel superiority trial will be conducted at four hospitals in China. A total of 440 lung cancer patients will be recruited in this study, who will be randomly assigned to the intervention group or the control group in a ratio of 1:1. Any of the target symptoms reaches the preset threshold (score ≥ 4), the patients will accept the symptom management advices based on the PRO. The patients in the control group will follow the current standard procedure of symptom management. The symptom management system is an electronic management system based on WeChat mini programs. All patients will be evaluated for symptoms through the lung cancer module of the MDASI lung cancer-specific scale on the day before surgery, days 1, 3, 5, and 7 after surgery, and once a week during the 12-week post-discharge period. Simultaneously, the EORTC QLQ-C30 scale will be used to evaluate patients’ quality of life at baseline and the fourth and twelfth week after the surgery. The mean number of symptom threshold events of the intervention and the control groups were compared by *t*-test, and the changes of PRO were compared by a mixed effect model. The primary endpoint has been set as the 12-week post-discharge period.

**Discussion:**

This study will test the feasibility of the symptom management system based on the mobile social media applet in postoperative caregiving and the efficacy of psychiatrist-assisted treatment and provide evidence in managing the symptoms of patients in the medium and long term.

**Trials registration:**

Trials registration number: ChiCTR 2200058876, Registered 18 April 2022

**Supplementary Information:**

The online version contains supplementary material available at 10.1186/s13063-024-07963-8.

## Background

Lung cancer is the malignant tumor with the highest morbidity and mortality worldwide. The incidence of lung cancer in China is more than 1/3 of the world’s reported cases [1]. With the increase in early lung cancer surgery, postoperative management and quality of survival have gradually become the focus of caregiving [2, 3]. Since the burden of postoperative symptoms and the incidence of postoperative complications are overwhelmingly high within 3 months after lung surgery, their quality of life (QOL) can be severely deteriorated by severe pain, cough, shortness of breath, fatigue, sleep disorders, and other physiological symptoms [4].

In addition to physiological symptoms, almost all cancer patients will also experience severe psychological disturbance from sorrow and distress. Related lung cancer studies have shown that the sadness and distress of patients with lung cancer are about 40%. Chinese patients are close to this level, and the emotions and symptoms are closely related to the quality of life [4–8]. Studies have shown that lung cancer patients held the highest incidence of psychological stress among all cancers [5, 9]. The symptoms of fatigue, pain, sadness, uneasiness, and distress, separately or corporately, constitute the most common psychological features within 3 months after the lung operation. Thus, the caregiving of patients with lung cancer needs to underpin the management of physiological symptoms and commit to tuning down the extent of distress and sad emotional symptoms. Practically, all the symptoms of postoperative lung cancer patients can be considered the parameters for further caregiving [10].

With the concept of “patient-centered care,” the patient-reported outcome (PRO), which is directly reported by the patient and details the patient’s health, functional status, and treatment experience with the exclusion of the interpretation from any other personnel, has been popularized in the caregiving process to abide with the “biological-psychological-social” medical model (Fig. 1) [11, 12]. Since the report directly from patients cancels the interferences and noises from the ones who are not the patients, PRO can mirror the real-time changes and manifestations of the patient’s symptoms, which, on the one hand, can more accurately guide the clinicians to choose more accurate intervention, on the other hand, can continuously evolve the treatment methods [13, 14].

**Fig. 1 Fig1:**
[figure not shown]
Process of symptom monitoring, early warning, feedback, and data collection; REDCap, research electronic data capture. CRF, case report form

Symptom management has been entrenched as the cornerstone of medical care. The symptom management based on PRO improved patients’ QOL, reached patient satisfaction, promoted the corporate decision-making of caregiver and patient, and benefited the clinical prognosis [14]. The previous studies on the efficacy of PRO-based symptom management only focused on single symptoms or were observational research [15–17], which had shown that patients with advanced chemotherapy could extend the survival time by 5.2 months(*P =* 0.03) with the PRO-based active symptoms monitoring in comparing with traditional passive monitoring. In addition, a randomized controlled study reported that physiological symptom monitoring within 1 month after lung cancer surgery made the threshold events and incidence of complications in the intervention group lower than those in the control group (0 vs. 2, *P* = 0.007; 21.5% vs. 40.6%, *P* = 0.019, respectively) [18, 19]. However, the study did not further address whether monitoring and managing psychological symptoms during the surgery could benefit the patients by prolonging survival time [20–25].

Although the application of PROs has gradually been promoted in the surgical treatment environment, very few clinical trials and studies were conducted on postoperative symptoms of lung cancer, containing physiological and psychological symptoms. Besides, the limitations of those previous studies included the following: (1) most were observational researches; (2) all of them focused only on managing physiological symptoms such as cough, pain, shortness of breath, and lack of patients with psychological symptoms such as sadness and distress; (3) all had an insufficient assessment on the symptoms; (4) there are even fewer studies on the Chinese population, which undermine paradigm change in the caregiving of lung cancer patients.

WeChat platform has become China’s leading online social network [26], providing real-time online person-to-person and group communication. So, we have designed this randomized controlled trial (RCT) to improve the effectiveness of postoperative caregiving for patients with lung cancer-based physiological (pain, cough, fatigue, sleep disorders, and shortness of breath) and psychological symptoms (sadness and distress) through the WeChat application, which can carry out the real-time monitoring of the early red-flag signs from various postoperative symptoms of the patients, and conveniently facilitate the clinicians to prescribe post-surgical palliative interventions (The operating mechanism is shown in Fig. 1). The PRO-based intervention methods will be used to manage patients with moderate and severe target symptoms in the intervention group, while current standard nursing methods will be used to care the patients in the control group. This trial will introduce a novel, safe methodology for managing medium and long-term symptoms in lung cancer patients. We will use the MD Anderson Symptom Inventory for lung cancer (MDASI-LC) [27] on the patients within 3 months before and after surgery to record the monitoring of target symptoms as well as related effects on the function of lung cancer patients. At the same time, the EORTC Core quality of life questionnaire (EORTC QLQ-C30) [28] was attempted to evaluate the quality of life of patients with lung cancer within 3 months before and after the lung operation. As a result, the aim of this study is to compare on the mean number of occurrences of target symptoms and survival quality of the trial participants who received PRO-based management to those of the patients undergoing the routine management.

## Methods

### Trial design

This multicenter, open-label, randomized, parallel-group, superiority trial will be conducted at four tertiary hospitals in two cities of Western China, including Tangdu Hospital, Daxing Hospital, the Affiliated Hospital of Shaanxi University of Traditional Chinese Medicine, and the Second Affiliated Hospital of Xi’an Medical College. The total number of lung cancer operations is approximately 5000 in these four hospitals yearly.

Participants who fulfill eligibility criteria will be randomly assigned with a 1:1 ratio to either a control group with current standard management or an intervention group with new management methods designed by the lung cancer specialist and psychological consultants from the four hospitals. This protocol abided by the standard protocol for clinical trials [29], and the flow chart of this trial is shown in Fig. 2.

**Fig. 2 Fig2:**
[figure not shown]
Flow chart of this parallel-group randomized trial

### Randomization and blinding

The stratified block randomization method will be used for this trial. The third-party statisticians will use the statistical software SAS9.4 PROC PLAN to generate random numbers and randomize the participating patients. Participants will be stratified by research center, and the appropriate segment lengths will be selected. Allocation of participants will be concealed using envelopes with consecutive numbers. The randomized numbers will be segmented, retained, and managed by the third party who will not be involved in the data collection. Each center assigned its participants according to the estimated number of participants and the enrollment sequence of each participant in that center. The random grouping table is pre-implanted into the WeChat applet. It will then be allocated to the intervention group or control group with a 1:1 ratio. Due to the nature of the intervention, the participating patients, specialist cannot be blinded. In order to reduce measurement bias, all personnel who assist in data collection and data analysts (the third party) will be blinded. As a result, unblinding will not occur in this trial.

### Study population

The recruitment will be conducted by the participating clinicians before surgery. Eligible patients should meet all inclusion criteria and should not meet any of the exclusion criteria. The inclusion criteria for participating in this trial include (1) the age between 18 and 75, (2) an imaging study showing that lung cancer is highly suspicious, (3) Eastern Cooperative Oncology Group (ECOG) PS 0–2 points [30], (4) normal primary organ function, (5) resectability with the estimated survival time beyond 6 months, (6) voluntariness to join the study with signed informed consent for participating the trial, and (7) compliance and cooperation during the trial.

The exclusion criteria were also settled as follows: (1) history of neoadjuvant therapy, (2) suffering from other malignant tumors, (3) inability to understand the research requirements, (4) existence of concomitant diseases or any other conditions that may confuse the results of the study or affect the subjects to complete the study, (5) history of psychotropic substance, alcoholism, or drug abuse, (6) possibility that may damage the subject or cause the subject to be unable to meet or perform the research requirements.

### Sample size calculation

The primary endpoint of this study was the mean number of symptom threshold events, which is calculated by averaging the number of target symptom threshold events per patient at each time point. The minimum important difference (MID) has been defined as the smallest difference in the scores of the PRO measure that patients perceive as beneficial or harmful and would lead the clinician to consider a change in treatment. The literature recommended that the minimum difference between the two groups should be ≥ 0.3 sd based on the clinical treatment comparison efficacy measured by PRO instruments [31]. To meet the MID (0.3 sd) with the PRO instrument for mean symptom threshold events, the sample size required for each group was 176 when rejecting the null hypothesis (difference between the two groups < 0.3 SD). A total of 352 samples are required in this study. According to the previous pre-investigation experience, the loss rate of follow-up and withdrawal was 20%; 220 patients should be the adequate number of participating patients for each group (176/0.8). Because this trial is an intervention study, the follow-up time is 3 months after major lung operations. The sample size calculation is based on the independent sample Student’s *t*-test, using a two-tailed test (*α* = 0.05, 1 − *β* = 0.8).

### Screening period

Before enrolling patients, researchers in each research center will receive standard operating procedure (SOP) training on research implementation methods and data collection. During the screening period, the data on participants’ demographics, physical examinations, current medical conditions, and history of comorbidities will be collected. Thoracic surgeons will mainly conduct the screening of participants. The surgeons will select patients who underwent surgery in the trial according to the inclusion criteria. Then, the clinical research associate will register all eligible patients for the trial. Patients who meet the screening criteria will be given a screening number. Then, if patients agree to participate in this trial, they will be given a subject ID and fill in MDASI-LC QLQ-C30 before surgery. Results in the screening period will be considered baseline data and will not be required to be repeated.

Surgeons who screen patients will be paid to increase their enthusiasm for work, and we will also invite as many surgeons in other inpatient areas as possible to participate in the trial to meet the samples required for the study.

### Intervention period

The questionnaire and parameters that will be measured to assess symptoms and life quality at each visit point are shown in Table 1. The participants will answer the MDASI-LC (ePRO) questionnaire through a WeChat applet within 1 week before surgery, the first, third, fifth, and seventh days after surgery, and every week after discharge till the 12th week. Participants can fill in the ePRO questionnaire by scanning the two-dimensional code and logging into their personal account after receiving the reminder message to fill in the WeChat applet. Moreover, the paper version of QLQ-C30 filled by the same participants within 1–2 days before the operation, 4 weeks, and 12 weeks after the operation will be submitted to the clinicians when the review process is completed. When one or more target symptoms (pain, cough, fatigue, sleep disorder, shortness of breath, sadness, and distress) occur and the score reaches the preset intervention threshold (above moderate, score ≥ 4) [32], the participants in intervention group will receive the standardized treatment suggestions in WeChat applet. At the same time, the participating specialists (thoracic surgeons) will also receive early alerting messages on their mobile phones to inform them to contact the patient through WeChat or phone within 24 h to provide the patient with management advices base on ePRO score, including, if not at all, consultation, education, drug guidance, and evaluation on the necessity of the trip to emergence, clinic, or hospital. In addition to the target symptoms, if the participants have other novel symptoms or their ePRO exceeds the threshold, standard treatment suggestions designed by the lung cancer specialist will emerge on the WeChat ePRO interactive interface [33–38]. The psychiatrists focus on the psychological symptoms (sadness and distress) of all patients in the intervention group. If the score is between 4 and 6 points, guidance to manage the psychological symptom will be given to the patients by the general specialist, while if the score exceeds 6 points, the patients will receive a telephone consultation with the psychiatrists. The measure used for symptom relief in the intervention group will comply with the latest guidelines and follow SOP manuals in all centers. In addition, the participating patients are not informed of the threshold level. Specialist will not receive warning messages from the PRO data of control group patients and will not access the patient data in the control group. During the trial, each center will provide the participating patients with on-site monitoring visits, telephone monitoring, and online or on-site guidance on managing the symptoms. If the patients concern their symptoms, they will decide whether to seek medical help based on their self-evaluation of their symptoms. The participating patients will be educated on how to seek medical help for severe symptoms through usual channels. All participants will be provided free long-term medical consultation via WeChat, which may promote participation and compliance.

**Table 1 Tab1:** Study plan detailing the procedures

**Study period**	**Screening**		**Intervention period**						
Visit	V1	V2	V3 (post-operation)	V4	V5	V7	V8	V9	
Visit day	− 1 (± 2 days)	Randomization/baseline	1 (± 1 day)	3 (± 1 day)	5 (± 1 day)	7 (± 1 day)	14 (± 3 days)	22 (± 3 days)	
**Screening/demography**									
Written informed consent	√								
Inclusion/exclusion criteria	√								
Demographics	√								
Physical examination, height, and weight	√								
Medical/current conditions	√								
ECOG (Eastern Cooperative Oncology Group)	√								
CCI (Charlson Comorbidity Index)							√		
**Intervention**									
Consultation, education, drug guidance, telephone consultation with the psychiatrists			√	√	√	√	√	√	
MDASI-LC (ePRO)		√	√	√	√	√	√	√	
QLQ-C30 (paper)		√							
Adverse events	√	√	√	√	√	√	√	√	
**Clinical characteristics**									
Surgical procedure, surgical approach, extent of surgery, stage, postoperative length of stay, postoperative chemotherapy							√		
**Study period**	**Intervention period**								
Visit	V10	V11	V12	V13	V14	V15	V16	V17	V18
Study day	29 (± 3 days)	36 (± 3 days)	43 (± 3 days)	50 (± 3 days)	57 (± 3 days)	64 (± 3 days)	71 (± 3 days)	78 (± 3 days)	86 (± 3 days)
**Screening/demography/baseline**									
Written informed consent									
Inclusion/exclusion criteria									
Demographics									
Physical examination, height, and weight									
Medical/current conditions									
ECOG (Eastern Cooperative Oncology Group)									
CCI (Charlson Comorbidity Index)									
**Intervention**									
Consultation, education, drug guidance	√	√	√	√	√	√	√	√	√
MDASI-LC (ePRO)	√	√	√	√	√	√	√	√	√
QLQ-C30 (paper)	√								√
Adverse events	√	√	√	√	√	√	√	√	√
**Clinical characteristics**									
Surgical procedure, surgical approach, extent of surgery, stage, postoperative length of stay, postoperative chemotherapy									

Interventions are based on participants’ ePRO scores, and if there is a target symptom score ≥ 4, there will be corresponding treatment

The adherence to the intervention measures will be evaluated at every given time. If the participants fail to comply with the intervention measures as required more than two times, it will be considered a severe violation of the study protocol and removed from the trial. If the participants have serious complications after the operation and cannot complete the PRO questionnaire with poor compliance or deliberately miss the questionnaire filling or request to withdraw, they will be stopped from further collecting the relevant data.

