### Control group

The patients in the control group do not receive any specific guidance on related symptoms except by completing the same questionnaire as the intervention group. The postoperative management of patients follows the current standard management in the hospital and after discharge. Following discharge, all the participants follow-up at the same time as the intervention group. At the same time, we encourage participants to actively seek medical help if necessary.

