## Results and measurements

### Primary outcomes

The main PRO tools in this study include MDASI-LC and EORTC QLQ-C30. MDASI-LC covers 16 lung cancer- and treatment-related symptoms as well as six disturbances to everyday life caused by symptoms and can be completed in five minutes. All items were scored on a scale of 0–10, with 0 as “no symptoms” or “no impact on life” and 10 as “the most serious level” or “complete impact on life.” Besides, the patients can have 24 h as the recall period before filling in MDASI-LC. Comparably, EORTC QLQ-C30 lays out 30 items, incorporating five functional dimensions, three symptom dimensions, six single symptom dimensions, and two total health status items. These can be done in 5 to 8 min with a recall period of 1 week. EORTC QLQ-C30 scores items 1–27 by the range of 1–4 points, with 1 as “no symptoms” or “no impact on life” and 4 as “the most serious level” or “complete impact on life.” Additionally, items 28 and 29 focus on health status assessment and can be scored by 1 to 7, with 1 as very poor and 7 as very good. For the evaluation, the severity of symptoms and function deterioration increases along the increments of the scores. Conversely, the higher the health score, the better the quality of life. Both scales have been widely used in China’s clinical setting with good reliability and validity [39, 40]. The main measurement indicators and follow-up schedule are shown in Table 1. The primary outcome of this study is the mean number of target symptom threshold events with discharge 12 weeks, which include pain, cough, fatigue, sleep disorders, shortness of breath, sadness and distress. According to published literature, patients with a symptom score of 4–6 can be classified as moderate and ≥ 7 as severe [33]. Thus, we presented the score of 4 as the threshold for intervention and the targeted symptom score of ≥ 4 as a threshold event in this trial. A score of 1 can be given if one of the target symptoms is recorded to be ≥ 4 in one follow-up and 3 if three target symptoms are graded as ≥ 4.

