### Secondary outcomes

The secondary outcomes of this study include the changes in PROs (symptom severity, daily function, and quality of life) and follow-up rates after discharge. The trajectory for PROs is defined as the average score of symptom severity for seven targeted symptoms and the average score of six MDASI-LC daily functional intervention items from baseline to 12 weeks after discharge. The trajectory for quality of life comes from the quality of life scale (EORTC QLQ-C30), including the measurement results at baseline and the 4th and 12th weeks after discharge.

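### Removal from the trial after more than two failures to follow the intervention measures depends on the primary outcome and falls essentially on the intervention arm

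*Protocol article*

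**What the plan says.** All references are to the protocol article.

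- **Removal rule** (Intervention period, below Table 1): "If the participants fail to comply with the intervention measures as required more than two times, it will be considered a severe violation". The stated consequence is that such a participant leaves the trial.
- **Trigger for the measures** (note to Table 1): "Interventions are based on participants’ ePRO scores, and if there is a target symptom score ≥ 4, there will be corresponding treatment".
- **Primary-outcome event** (Primary outcomes): "the targeted symptom score of ≥ 4 as a threshold event in this trial".
- **Controls** (Control group): "The patients in the control group do not receive any specific guidance on related symptoms except by completing the same questionnaire". Both arms fill in the same forms.
- **Separate data-stop rule** (same paragraph as the removal rule): for patients with serious complications who cannot complete the questionnaire, patients who deliberately miss forms and patients who ask to withdraw, "they will be stopped from further collecting the relevant data". This rule is not tied to an arm.
- **Analysis** (Statistical analysis): the protocol set leads. The full analysis set is also used, missing data are multiply imputed, and the main sensitivity analysis compares data without missing values with imputed data.

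The article does not say that questionnaires are still requested after removal.

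**The concern.** The removal rule combines two features that are harmful together. It acts after randomisation in essentially one arm, and the exposure that makes removal possible is the outcome itself. A patient whose symptoms never reach the threshold has nothing to fail. A patient who reaches it week after week has many chances. Taking out the second kind of patient lowers the average event count of those who remain in the intervention arm, while comparable controls stay in.

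At stake is the validity of the leading comparison in a superiority trial: part of any benefit seen in the protocol set could come from selection. This is also a matter of data collection that a later analysis plan cannot repair. Outcomes not requested after removal cannot be recovered.

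**Working it through.** **1. The plan's own figure.** Inputs from Sample size calculation: difference 0.3 SD, two-sided α = 0.05, power 0.80, 20% loss.

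- Normal approximation: n = 2(1.96 + 0.84)²/0.3², rounded up to 175 per group.
- Exact two-sample t-test: 175.4, rounded up to 176. This agrees with the article.
- After loss: 176/0.8 = 220 per group. This also agrees.

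The sample size is not in dispute. The 20% allowance protects power; it does not protect against selective loss.

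**2. Number of occasions.** The post-operative MDASI-LC visits in Table 1 are V3, V4, V5, V7 and V8 to V18: 4 + 11 = 15.

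**3. Chance of removal.** Let k be the number of forms with a target symptom at 4 or more, and q the chance of non-compliance at each. Assume one possible failure per alerted form, independent between forms. Removal needs at least 3 failures:

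P(removal) = 1 − Σ(j = 0 to 2) C(k, j) qʲ(1 − q)ᵏ⁻ʲ

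Example, k = 10 and q = 0.20: 1 − (0.107 + 0.268 + 0.302) = 0.32.

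| k | q = 5% | q = 10% | q = 20% |
|---|---|---|---|
| 2 | 0 | 0 | 0 |
| 3 | 0.01% | 0.1% | 0.8% |
| 6 | 0.2% | 1.6% | 9.9% |
| 10 | 1.2% | 7.0% | 32% |
| 15 | 3.6% | 18% | 60% |

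For any fixed q, removal becomes more likely as k rises. For controls it is zero, because no measures are due.

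**4. Bias in the protocol set with no true effect.** Simulation with 220 per arm, 15 forms and a beta-binomial number of alerted forms per patient. Alerted forms stand in for the event count. Patients with 3 or more failures are dropped from the intervention arm only. Bias is the shift in the mean of the retained patients, in SD units. Both q and the distribution of alerted forms are assumptions.

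| Mean alerted forms | q | Removed | Spurious benefit | Type I error |
|---|---|---|---|---|
| 3.8 to 4.5 | 5% | 0.2 to 0.3% | about 0 SD | 5% |
| 3.8 to 4.5 | 10% | about 2% | 0.03 SD | about 6% |
| 3.8 to 4.5 | 20% | 7 to 10% | 0.12 to 0.15 SD | 25 to 35% |
| 7.5 | 10% | 5% | 0.05 SD | 7% |
| 7.5 | 20% | 22% | 0.24 SD | 66% |
| about 10 | 10% | 9% | 0.06 to 0.07 SD | 10% |
| about 10 | 20% | 34% | 0.27 to 0.30 SD | 73 to 77% |

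Ranges within a row reflect different assumed spreads of alerted forms between patients. In the runs with a mean of 3.8 to 4.5, removed patients had averaged about 9 to 10 alerted forms.

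Type I error follows from the bias. With 8.6% removed and a bias of 0.124 SD, SE = √(1/220 + 1/(220 × 0.914)) = 0.0976. Then 0.124/0.0976 = 1.27, and the chance of a significant result in favour of the intervention is Φ(−1.96 + 1.27) ≈ 0.245.

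**5. If removed patients are kept with the data they had.** A further null simulation, with an assumed logistic event model and a mean of 1.5 to 8.6 alerts, kept them in the comparison. Using their average before removal, the bias was about 0 SD with flat symptoms and up to 0.10 SD against the intervention with declining symptoms. Summing events without imputation, the spurious benefit was at most 0.15 SD.

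**The case against.** **The size is not known.** This stands. The largest figures need about 10 alerted forms of 15 together with 20% non-compliance, and the article supports neither. Its Background cites 0 versus 2 threshold events in an earlier trial; at 2 occasions removal is impossible. That trial covered physiological symptoms over one month, against seven symptoms over 12 weeks here, so it is weak evidence. Removing 34% of an arm would also exceed the planned 20% loss. A reader might infer a type I error above 70%; that is one corner of the range, not an estimate.

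**The patients are not lost altogether.** This stands in part. Someone with three failures has at least three post-operative MDASI-LC forms on the counting used here, more than the two required besides baseline, and the full analysis set may keep those data. The minimum also asks for a postoperative QLQ-C30, first due at V10, so an early removal could still fail it. Outcomes after removal would rest on imputation. Imputation from the recorded scores may help, but it assumes that non-compliers resemble other patients with similar scores. The stated sensitivity analysis does not test that.

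**The data-stop rule hits one arm.** A reader might infer this, but the text does not support it. The rule covers both arms and is narrower than any complication or any missed form: the patient must be unable to complete the questionnaire, miss it deliberately or ask to withdraw. It adds informative missing data, and any imbalance would be indirect.

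**Controls could be removed too.** Table 1 lists the MDASI-LC under Intervention, so the measures might include filling in forms. Even so, only the intervention arm has the additional, score-triggered ways to fail.

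**Inclusion criterion 7 adds to the problem.** A reader might infer this from "compliance and cooperation during the trial". The criterion applies before randomisation and reads naturally as expected cooperation, so it cannot unbalance the arms.

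**Conclusion.** The concern holds in a bounded form. The removal rule makes exclusion depend on the primary outcome, essentially in the intervention arm, and the protocol-set comparison is then biased towards the intervention. The direction is firm provided that removed patients leave the protocol set, which is the natural reading of a severe violation followed by removal.

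The size is not firm. It runs from negligible at 5% non-compliance per alert to about half the design effect at most (0.12 to 0.15 of 0.3 SD) at 20% with 4 to 4.5 alerted forms. It approaches the whole design effect only under a heavy alert burden. The documents do not support carrying this size or direction over to the full analysis set: there the bias depends on how the event count is averaged or summed and how missing forms are imputed, and it can run either way.

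**What to change.** - Replace removal from the trial with recording non-adherence as a protocol deviation. Whether measures continue to be offered to such a patient is a separate matter that this point does not address.
- Keep requesting the MDASI-LC and QLQ-C30 through V18 in both arms. Stop only when the patient withdraws consent to data collection. Apply the same principle to the separate data-stop rule, recording the reason whenever a form cannot be obtained.
- Analyse these patients in the arm to which they were randomised, and add a sensitivity analysis that lets unobserved outcomes be worse than the imputation model predicts.

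**Cost.** A short amendment, more incomplete records to handle, and some continued work: applet reminders exist for the MDASI-LC, but non-responders after discharge are contacted personally by phone or WeChat, and the QLQ-C30 is on paper. The sample size does not change. If all 220 per group were observed, power at 0.3 SD would be about 88% instead of 80%.

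The article anticipates the last visit on 30 June 2023, so an amendment may come too late for some patients. For them, report removals by arm with time, reason and event count before removal, and include the data collected up to that point.
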